**Figure 2 F2:**
[figure not shown]
Group sessions contents. SPACE FOR, COPD, Self-management Programme of Activity, Coping and Education for Chronic Obstructive Pulmonary Disease.

We anticipate that some participants may not be able to attend all the group sessions or may be unable or unwilling to attend the research centre. In this instance, we will accommodate the participant in another session (with permission of that group) or via videoconferencing. If this isn’t possible a telephone contact will be conducted instead.

#### Staff training and intervention fidelity

In total, eight HCPs have been trained to deliver the SPACE FOR COPD maintenance programme by a health psychologist and a specialist nurse. All attended a 1-day training course (supplemented with written material and DVD tutorials to take away) to learn the structure of the structure of the group sessions, the SPACE for COPD manual and MI skills.

The agenda covered: MI skills, introduction to the facilitator manual and review of SPACE FOR COPD manual, practical workshop, group facilitation, learning outcomes revisited and trial management.^6^ of the HCPs had previously received additional MI training and all had experience in delivering PR.

A teleconference will be held between all the facilitators across the two sites prior to and following the first intervention session to problem solve and share experiences. The teleconference will then be continued on a regular basis to maintain the flow of the maintenance procedure and to provide peer support.

Quality assurance will be undertaken to assess delivery of intervention content and educational style. Intervention fidelity checklists for the intervention facilitators have been adapted from a previous study.^18^ One session per self-management group will be peer-observed and the checklist will be completed. Each site will observe the opposite site’s group. Facilitators will complete fidelity checklists at the end of each session. These will assess: content covered, managing groups and adhering to MI principles.

For the trial, external auditing may take place at the discretion of the sponsor (UHL NHS trust).

### Study outcomes

The assessments described below will be conducted at baseline, 6-month and 12-month visits and completed by a blinded assessor, unaware of the group allocation. Due to the impact of COVID-19 restrictions, assessment visits and consent may be completed over the phone for all data other than physical tests where this is not possible (ie, spirometry/walking tests). Consent form for patients shown in online supplemental file 1.

10.1136/bmjopen-2021-055513.supp1Supplementary data

### Primary outcome

#### Endurance capacity

The primary endpoint at 12 months is endurance capacity measured by the Endurance Shuttle Walk Test (ESWT), expressed in seconds. The ESWT is a walking field test that has been found to be safe, valid and reproducible among patients with COPD.^23^ The minimal clinically important difference (MCID) for this population is estimated to be between 174 and 279 s.^24^

### Secondary outcomes

#### Exercise capacity

Incremental Shuttle Walking Test (ISWT) will be used to measure the maximal exercise capacity following the test protocol published by Singh *et al*.^25^ The MCID in walking distance is between 35.0 and 36.1 m.^26^

#### Chronic Respiratory Questionnaire-self reported

Chronic Respiratory Questionnaire-self-reported (CRQ-SR) is a valid and reliable self-administered tool to assess health-related QoL (HRQoL) in people with chronic lung diseases.^27^ It assesses four domains with MCID defined as a mean change of 0.5 for each domain. The domains are dyspnoea (five questions), fatigue (four questions), emotional function (seven questions), and mastery (four questions) and are scored on a 7-point scale per question.

#### Chronic obstructive pulmonary disease assessment test

Chronic assessment test (CAT) is a tool developed to assess and monitor COPD symptoms and changes in patient’s health status.^28^ It is responsive in both short-term and long-term assessments and is used widely in PR programmes for patients with COPD.^4^ It consists of eight simple questions which cover ‘cough, phlegm, chest tightness, breathlessness going up hills/stairs, activity limitation at home, confidence leaving home, sleep and energy’ on a 5-Likert scale. Scores ranges from 0 to 40 indicating none to very severe impact on health status.

#### EuroQol-five Dimensions-five Levels

The EuroQol-5 Dimensions-5 Levels (EQ5D5L) is a self-administered non-disease specific tool used to measure HRQoL and is developed by the EuroQol group.^29^ This measures health on five dimensions (mobility, self-care, usual activities, pain or discomfort, and anxiety or depression) and a tariff is available for deriving a single utility score based on time trade-off utility scores. It also includes a visual analogue scale on which individuals rank their health today from 0 (worst health) to 100 (best health).^30^

#### Patient activation measure

The NHS long-term plan^31^ supports the engagement of patients to self-management, which is a vital key to our trial, where the 13-item patient activation measure (PAM-13) tool can be used as recommended by NHS.^32^ PAM-13 tool assesses participants’ knowledge, skill and confidence for managing their own health and healthcare.^33^It is valid and reliable tool that defines four levels of activations ranges from low level to high level of activation.

#### Anxiety and depression

The Hospital Anxiety and Depression Scale (HADS) will be used to measure anxiety and depression.^34^ It is a responsive tool and it has been tested on patients with COPD in several study settings.^35^ It has 14 questions to measure anxiety and depression (seven questions for each scale). Minimum and maximum scores for each scale are 0–21, respectively. The MCID is a mean change of 1.5 points for each scale.^36^

#### Physical activity monitoring

The participants will be asked to wear a physical activity monitor after each visit (wGT3X- ActiGraph, Pensacola, Florida, USA), for seven consecutive days, except during sleeping and water-based activities. The monitor will be activated automatically for that period and doesn’t require the participant to turn it on or off. It is a small device attached to an elastic belt to be worn on the waist and placed at the mid right hip. It will enable us to retrieve daily activity bouts, intensity of activities and step counts. Activity monitors can be posted out if assessment is performed over the phone.

#### Pulmonary function testing

Pulmonary function will be assessed by hand-held spirometry called Vitalograph Pneumotrac 6800 (Vitalograph, Buckingham, UK) to confirm and assess the severity of COPD. The test will be performed if there was no previous test done within a 3 month period. The spirometry test will be done following standard guidelines.^37^ The device will be calibrated on daily basis and participants will be assessed for contraindications prior to performing the test.

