**Methods and analysis:**

A prospective, multicentre, single-blinded randomised controlled trial requiring 116 participants with a clinical diagnosis of COPD who have finished PR within 4 weeks will be randomised 1:1 to either a usual care group or a SPACE FOR COPD programme group. The intervention comprises a home-based manual and 4, 2-hour group sessions adopting motivational interviewing techniques over 12 months. The primary outcome is endurance capacity measured by the Endurance Shuttle Walking Test at 12 months. Secondary outcomes are: maximal exercise capacity, health-related quality of life, mood, patient activation, physical activity, lung function and healthcare costs. The measures will be taken at baseline, 6 and 12 months. Patient interviews and staff focus groups will be conducted to explore barriers, facilitators and views about the intervention at the end of the study. A framework analysis will be used for the interpretation of qualitative data.

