### Aims

The overarching aim of the study is to assess whether a self-management maintenance programme (SPACE FOR COPD), delivered on PR discharge, preserves the anticipated gains made in exercise tolerance and mental well-being at 12 months, compared with usual care alone.

The primary aim is:

To compare endurance walking distance at 12 months in those who have completed the SPACE FOR COPD maintenance programme compared with usual care.

The secondary aims are:

To compare the following variables at 12 months in patients who have completed the SPACE FOR COPD^©^ maintenance programme versus usual care:Maximum walking distance.QoL.Anxiety and depression.Physical activity.Symptoms (breathlessness, fatigue, sputum production, cough, sleep, chest tightness).Patient activation (knowledge, skills and confidence to manage COPD).Forced expiratory volume in 1 s.To measure adherence to the SPACE FOR COPD maintenance programme in terms of sessions attended, completion of the programme and manual diary entries.To collect data for future health economic analysis in both groups; including hospital admissions, healthcare contacts, personal social service costs and patientborne expenditure.To understand the patient experience of SPACE FOR COPD; to identify facilitators and barriers of the package to maintain health and well-being.To work with staff, managers and commissioners involved in the delivery of SPACE FOR COPD as a maintenance option to explore how, if successful, this programme could be rolled out more widely.To use data pre-PR, where available, to evaluate the effectiveness of the initial PR programme and its impact on the maintenance rehabilitation programmes outcomes.

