### Randomisation and blinding

Eligible participants will be consented and randomised using a concealed allocation web-based programme (https://www.sealedenvelope.com/). Randomisation will be 1:1 to either usual care (control) or the SPACE FOR COPD maintenance programme (intervention). Randomisation codes will be blocked per site, providing even numbers of control and intervention patients at each site and a sufficient number of participants for the intervention group sessions to run. Due to the nature of the intervention, the participants and intervention facilitators will not be blinded to group allocation. However, the assessors will be blinded to group allocation. Other blinded assessors are in place in case of blinding exposure by first blinded assessor. Any unintentional unblinding will be documented.

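### The three-month spirometry waiver is not confined to baseline, so FEV1 at 6 and 12 months may be missing or come from a test outside the trial

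*Protocol article*

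**What the plan says.** Four parts of the protocol article bear on this.

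- **FEV1 is an outcome.** The Aims section introduces its secondary comparisons with "To compare the following variables at 12 months in patients who have completed the SPACE FOR COPD" and includes "Forced expiratory volume in 1 s" in the list. The abstract agrees: "Secondary outcomes are: maximal exercise capacity, health-related quality of life, mood, patient activation, physical activity, lung function and healthcare costs".
- **It has a schedule.** The abstract continues: "The measures will be taken at baseline, 6 and 12 months". Trial design and setting gives the same three visits and no others.
- **It has an assessor.** Study outcomes opens with "The assessments described below will be conducted at baseline, 6-month and 12-month visits and completed by a blinded assessor, unaware of the group allocation". Spirometry is among the assessments that follow. Physical tests are excepted from the option of a telephone visit.
- **It has a waiver.** Pulmonary function testing names a specific hand-held device, calibrated daily, gives the purpose as "to confirm and assess the severity of COPD", and then states: "The test will be performed if there was no previous test done within a 3 month period". It does not say at which visits this applies, and it sets no condition on the setting, device or assessor of the previous test.

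**The concern.** Accepting a recent result is reasonable when spirometry only confirms the diagnosis and describes severity at entry. It is not suitable for an outcome, which should be measured at the same time, in the same way and by a blinded assessor in both arms. The article has one spirometry section and it serves both purposes, so the waiver as written also reaches the outcome visits.

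At stake is the comparability of FEV1 between arms. Spirometry depends on effort and coaching, so the setting, the device and the time since an exacerbation can all affect the value. Whether a participant has had a recent test outside the trial depends on healthcare contact after randomisation. The Introduction hopes that the programme may reduce repeat rehabilitation and readmissions, and Patient adherence expects some of both to occur. If such contact differs by arm, the share of waived tests may differ too. The Data analysis section uses secondary outcomes in a 12-month between-group comparison and in a repeated-measures analysis, so both would be affected.

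**Working it through.** The article gives no figure for this point that could be reproduced. The check is one of dates.

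**Inputs**
- Trial visits: months 0, 6 and 12 (Trial design and setting).
- Look-back of the waiver: 3 months (Pulmonary function testing).
- Visits to which the waiver applies: not stated, so all three as written.

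**Step 1: the window at each visit.** Window opens at visit month minus 3.

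| Visit | Window opens | Previous trial visit | Is that visit inside the window? |
|---|---|---|---|
| Baseline | 0 − 3 = month −3 | none | no |
| 6 months | 6 − 3 = month 3 | month 0 | no |
| 12 months | 12 − 3 = month 9 | month 6 | no |

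**Step 2: where a qualifying test can come from.** The gap between successive trial visits is 6 − 0 = 6 and 12 − 6 = 6 months, both longer than 3. With visits on schedule, the trial's own previous test can never trigger the waiver. A test that does must come from outside the trial assessments, dated between months 3 and 6 or between months 9 and 12.

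**Step 3: what happens to the outcome.** The article says when the test is done, not what is recorded when it is waived. There are two possibilities.
- *The outside value is used.* It may be up to 3 months early. The named device and the blinded assessor apply to trial assessments and are not assured for it.
- *No value is recorded.* FEV1 is then missing at that visit, and the reason is recent healthcare contact. Data analysis assigns missing data to multiple imputation, which would have to account for that reason.

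In either case the visit lacks the scheduled, blinded measurement that the abstract and Study outcomes describe.

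**Step 4: baseline is different.** A test from month −3 onward precedes randomisation. It may predate or fall within rehabilitation, which makes it a less precise baseline value, but allocation cannot have influenced whether it exists. The concern about differences between arms is confined to the 6- and 12-month visits.

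**Step 5: size.** The number of affected values is the number of FEV1 assessments multiplied by the share with an outside test in the window. The article gives no such share and no basis for assuming one, so no count or bias is calculated.

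**The case against.** The strongest reply is that the waiver was meant for baseline only. The stated purpose, "to confirm and assess the severity of COPD", comes immediately before it, and confirming a diagnosis belongs to entry. This reading is plausible and would remove the problem. But the text does not say so, and no other section describes how the FEV1 outcome is obtained. If baseline was the intent, the fix simply records it.

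A second reply is that an article leaves operational detail to the full protocol. That would answer a complaint about something left out. Here a stated rule does not fit a stated schedule and a stated assessor.

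A third is that a specific exception can qualify a general opening statement, so the two sections need not strictly contradict each other. That is fair. The clearest tension is with the visit schedule for this one measure. Where the test is performed at a trial visit, nothing suggests that it is unblinded.

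A reader might go further and infer that an unblinded routine-clinic FEV1 is to be entered as the 12-month outcome. The document does not support that. It never says that an old value is carried into the outcome. It does not say who performs outside tests or whether they would know the allocation. On blinding, it says only that "the participants and intervention facilitators will not be blinded to group allocation". The most that follows is that blinding is not assured. Nor does the document show that recently unwell participants are more likely to have such a test, or give any direction of bias.

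**Conclusion.** The point holds as a wording fault with a possible effect on one secondary outcome. As written, the waiver reaches the 6- and 12-month visits. On schedule it can be triggered there only by a test from outside the trial. FEV1 is then either missing or up to 3 months early and not assured to be blinded or on the trial device. Because outside testing depends on post-randomisation healthcare contact, the effect could differ by arm.

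This rests on two assumptions: that the waiver is applied as worded, and that visits take place about on schedule. It does not show what the authors intended or that any outside value has been used.

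The size is unknown. The 3 months is a limit on timing and should not be read as a measure of error in FEV1. The primary endurance walking outcome is not affected. This is a minor point, worth raising because it is cheap to correct.

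**What to change.** Reconcile Study outcomes with Pulmonary function testing, as follows:

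- Confine the three-month waiver to describing COPD severity at baseline.
- Have the blinded assessor measure FEV1 on the trial device at every in-person 6- and 12-month visit, whatever tests have been done elsewhere.
- Keep outside values out of the between-group FEV1 comparison. Where a visit is held by telephone and no test is possible, treat FEV1 as missing.

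The cost is a sentence or two of text and a few additional hand-held tests within visits already scheduled, on equipment already specified.

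The Ethics and dissemination section dates the first recruitment to October 2019, so some 12-month visits were due before the article appeared in April 2022. If outside values have already been recorded at follow-up, flag each with its date and source, report the number by arm, and make the comparison without them.

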#### Patient adherence

The exercise diary entries embedded within the SPACE FOR COPD manual will be used to measure adherence to the home-based maintenance programme part. Also, group session attendance will be recorded and calculated as total attendance rate. A 75% cut-off will be considered as a programme completion at the end of the trial. To reduce lost to follow-up, we will reimburse participants’ travel expenses. Where patients drop-out of the SPACE FOR COPD maintenance programme, we will still collect 6-month and 12-month assessment data if consent is still in place.

Adherence to the programme is critical. To improve adherence we will be as flexible as possible with sessions and closely monitor home exercise diaries. If a participant is unable to attend a session we will offer attendance of the same session within another group (with the verbal consent of that group) or via teleconference as the preferred option or a one to one contact. We will send out text/email/postal reminders for group sessions and appointments. We expect that some patients may readmit to hospital and attend PR again. This will be documented but we would not deny further postexacerbation PR in these patients, in accordance with UK guidelines.^20^

#### Resource use questionnaires

Structured resource use questionnaires have been designed for the purpose of this trial and piloted prior to use. These will collect information on the number of hospital inpatient and outpatient episodes; community health and social care costs; and changes to employment status. Patient-borne costs associated with hospital visits (eg, travel, dependant care, time off work) and out-of-pocket expenditure on products or equipment (eg, walking shoes) will also be recorded. Questionnaires will be administered to coincide with visit times that is, baseline, 6 months and 12 months.

#### Interviews with patients

Semistructured, face-to-face interviews will be conducted with patients in the intervention group: both completers and non-completers. This will be optional and there will be a separate box on the patients’ consent form for participants to opt in (online supplemental appendix 1). The aim of the interview is to give a more complete picture of the perspective of the subjects of the study^38^; we will be adopting an interpretativist approach.^39^At the end of the 12-month period (or before if a patient decides not to continue the group sessions), we will conduct an interview to explore their experiences of using the new maintenance manual at home, the group sessions and the research process.

Participants will be recruited using a purposeful sampling technique: maximum variation sampling strategy. These interviews (n=10–20 or until data saturation) will be organised and completed by a qualitative researcher who has not been involved in delivering the intervention. Indicative interview schedules will be used and so may be refined following the first 4–5 interviews. The purpose of this qualitative work is to explore perceptions of SPACE FOR COPD as a maintenance strategy.

We will explore (Intervention) patients’ experiences of SPACE FOR COPD, identifying barriers and facilitators to the maintenance of well-being facilitated by the programme and to examine whether the sense of abandonment is lessened. The interview schedule will be flexible enough to allow completely unanticipated issues to arise. The interviewer will have adequate experience and expertise to deal with difficult situations (eg, distress).

The patient interviews will take place at the point of trial completion (at 12 months or earlier if there is attrition). We are interested in the views of patients who do not complete the programme also. Interviews will take place either in hospital or in the patient’s home or via phone or video call for those unable to attend the research centre.

#### Focus group for HCPs

We will also conduct focus groups with staff involved in delivering the intervention, to understand the relative burden and benefits of this new intervention to their services. Two focus groups with 5–10 participants per group will be organised and conducted by a qualitative researcher who has not been involved in delivering the intervention.

Staff will attend a semistructured focus group at their workplace and the findings of these will inform the training needs of those providing the intervention. They will also help to ensure that the intervention is moulded in a way that is compatible with existing models of service provision and working practices, which may help to maximise the likelihood of uptake locally and nationally.

#### Pre-PR data

Baseline data from the initial PR will be collected, where available, to evaluate the effectiveness of the PR and its impact on the SPACE FOR COPD maintenance programme. Data will include: ESWT, ISWT, CRQ-SR, CAT, HADS as these measures are routinely collected as part of PR.

### Sample size

The power calculation (for a continuous outcome superiority trial) is based on the primary outcome measure. We require 116 patients for an 80% chance of finding a 184 s (SD: 282 s) difference in the ESWT time between groups at 12 months (at the 5% level). The 184 s was the between group difference reported in the original primary care SPACE FOR COPD study^14^ and is similar to the suggested MCID range for this outcome (174–279 s).^24^ This number includes expected attrition of 20%.

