### Data analysis

#### Quantitative analysis

All data will be analysed on an intention-to-treat basis using SPSS software (V.26.0, IBM). We will conduct a separate per-protocol analysis for those who complete the intervention. Continuous variables will be presented as mean (SD), categorical variables as frequencies (percentages). All data will be assessed for outliers, normality and analysed using appropriate parametric and non-parametric statistics. To test the primary outcome, the difference between the two groups for the ESWT time will be analysed at 12 months using an independent t-test (or non-parametric equivalent).

Secondary outcome measures will be analysed in the same way. We will also look at changes in all outcomes in individual participants over time (ie, pre-PR, post-PR, 6 months and 12 months) using a repeated measures analysis of variance (or non-parametric alternative). Significance will be set at p<0.05 and differences between groups will be expressed as mean (95% CIs). Analysis will take into account the baseline values and adjust for potential confounders (eg, age, disease severity). Missing data will be corrected for by multiple imputation. Interim data may be made available for abstracts but unmasking will not occur.

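### The sample size does not follow from its own inputs: they give about 96 patients for 80% power, while the stated 116 gives about 87% power

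*Protocol article*

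**What the plan says.** The Sample size section of the protocol article describes a superiority calculation for a continuous primary outcome: "We require 116 patients for an 80% chance of finding a" 184 s difference (SD 282 s) in ESWT time between groups at 12 months, at the 5% level. It gives the source of the effect ("The 184 s was the between group difference reported in the original primary care SPACE FOR COPD study") and closes with "This number includes expected attrition of 20" per cent. Attrition is the only allowance named.

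The abstract repeats the figure as a requirement: "single-blinded randomised controlled trial requiring 116 participants". The Randomisation and blinding section gives 1:1 allocation. The Quantitative analysis section names an independent t-test, or a non-parametric equivalent, for the primary comparison. It adds "Significance will be set at p<0.05 and differences between groups will be expressed as mean (95% CIs"), which fits a two-sided 5% test.

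**The concern.** The paragraph gives every input that a two-sample calculation needs and then a total that those inputs do not produce. This is not a matter of detail left to another document, because what is printed is complete and does not add up.

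At stake is what the trial can be said to be powered for. If the inputs are right, the power is misreported. If 80% is right, then the SD, the difference, the loss allowance or an undisclosed inflation differs from what is printed. A neutral result would be discussed against the wrong power. The amount of missing primary data the trial can absorb would also be misjudged. That margin matters here, because the Study outcomes section allows telephone assessments for everything except spirometry and the walking tests.

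**Working it through.** **Inputs.** Difference Δ = 184 s, SD σ = 282 s, power 80%, level 5%, attrition 20% included in the total (Sample size); 1:1 allocation (Randomisation and blinding); independent t-test (Quantitative analysis). Sidedness is not stated. Two-sided is assumed, which fits the 95% confidence intervals; one-sided is tried below. The SD is read as the common within-group SD, so the standardised difference is 184/282 = 0.652.

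**Attempt to reproduce 116.**

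- Normal approximation: n per arm = 2 × (1.96 + 0.8416)² × (282/184)² = 36.9, so 37. Evaluable 74; 74/0.8 = 92.5, so 93, or 94 for equal arms.
- Exact t-test (noncentral t): n per arm = 37.9, so 38. Power is 79.1% at 37 per arm and 80.2% at 38. Evaluable 76; 76/0.8 = 95, or 96 for equal arms.

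The stated 116 is not reproduced: 116 − 96 = 20 patients, and 20/96 = 21%.

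**Power that 116 gives.** 116 × 0.8 = 92.8 evaluable, 46.4 per arm. Exact t-test power is 87.2% at 46 per arm and 87.5% at 46.4. The normal approximation gives 88.2% at 46.4.

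**Other readings of the stated inputs.**

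| Reading | Total randomised |
|---|---|
| Attrition added as ×1.2 instead of ÷0.8 | 89 to 92 |
| One-sided 5% | 75 |
| Rank test, relative efficiency 0.955 | 100 |
| Rank test, worst-case efficiency 0.864 | 110 |

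**Departures from the stated inputs.**

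| Change | Total randomised |
|---|---|
| Difference of 174 s (lower end of the MCID range) | 105 to 108 |
| 85% power | 108 to 110 |
| 90% power | 125 to 128 |
| Two-sided 2.5% level, normal approximation (45 per arm) | 113 |
| Two-sided 2.5% level, exact t-test (45.9, so 46 per arm; 46/0.8 = 57.5, so 58 per arm) | 116 |
| Attrition applied twice, 74/0.8/0.8 = 115.6 | 116 |

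The last two rows reach 116. One contradicts the stated 5% level, and the other would be a slip.

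**What would have to differ for 116 to mean 80% power.** With 46 evaluable per arm and the exact t-test, one of these would have to hold:

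- an SD of about 312 s instead of 282 s; or
- a difference of about 167 s instead of 184 s.

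With both as stated, 76 evaluable out of 116 is 65.5%, so 80% power survives the loss of about 34% of primary outcome data.

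**The case against.** The strongest defence is that the discrepancy is conservative. On the stated inputs 116 gives more than the promised power, neither the estimate nor the type I error depends on it, and the primary result will be read from a 95% confidence interval rather than from planned power. All of that stands. It makes this a reporting correction and not a threat to validity.

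A second defence is that the article condenses a fuller protocol, which may record a further allowance. The intervention runs in groups of 5 to 10, so a design effect is conceivable. For illustration only, with groups of 10 and an assumed intracluster correlation of 0.05, the intervention arm inflates by 1 + 9 × 0.05 = 1.45, and 38 × (1 + 1.45)/0.8 is about 116. The correlation is an assumption that the article does not give, and the Sample size section names attrition alone. If such an allowance was made, the paragraph leaves out part of the basis for its own number and still needs correcting.

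Third, the cause cannot be identified. Double attrition, a 2.5% level, a larger SD and a clustering allowance all land on or near 116. That also stands, and no particular cause is asserted here. It follows that 80% may have been the genuine target and another figure may be the misprint.

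**Conclusion.** The concern holds. On the printed inputs, read as a two-sided 5% t-test with a common SD and 1:1 allocation, 80% power needs 95 to 96 randomised (93 to 94 by the normal approximation). The stated 116 with 20% attrition gives about 87% power. The choice of formula does not explain the gap. A one-sided test widens it, and the planned non-parametric fallback closes it only in part. The document does not show which figure is wrong. On its own inputs the trial is larger than it needs to be, not smaller, so the consequence is a misreported design basis for the primary outcome and not a loss of power.

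**What to change.** The sponsor should first recover the calculation that produced 116, then correct the Sample size paragraph in one of these ways:

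- **If the printed inputs are right and 116 is kept:** state that 116 randomised, about 93 evaluable after 20% attrition, gives about 87% power to detect 184 s (SD 282 s) with a two-sided 5% t-test.
- **If 116 came from something not printed:** state it, whether that is a different SD or difference, a different significance level, a clustering allowance for the session groups, or extra loss of walking tests at telephone visits, with its value.
- **If 80% power on the printed inputs is the true target:** the number required is 96, and both this section and the abstract should say so.

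In each case give the evaluable number per arm and the sidedness of the test. The cost is rewording one paragraph, plus the abstract if the number changes. Recruitment need not change.
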